**Fig. 1. S3.F1:**
[figure not shown]
**Schematic overview of the study procedure**. CCRT, 
computerized cognitive remediation therapy; HD-tDCS, high-definition transcranial 
direct current stimulation; MCCB, MATRICS Consensus Cognitive Battery; MRI, 
magnetic resonance imaging. T0, baseline; T1, after 10 sessions; T2, after 20 
sessions; T3, after 6 months of follow-up; mPFC, medial prefrontal cortex. The 
labels Fp1, Fp2, F7, and F8 denote standard electrode positions according to the 
international 10-20 system, indicating the placement of the cathode electrodes 
for the HD-tDCS montage.

### 2.2 Recruitment and Eligibility Criteria

This trial will be conducted at the Second Affiliated Hospital of Xinxiang 
Medical University. Eligible individuals will adhere to the following inclusion 
criteria: (1) According to the Diagnostic and Statistical Manual of Mental 
Disorders, Fifth Edition (DSM-5), the individual meets the clinical criteria for 
schizophrenia. (2) Patients who maintain stability with oral antipsychotic 
medication are defined by the following criteria: a score of ≤5 on the 
items of exaggeration, delusion, suspiciousness/victimization, and hallucinatory 
behavior in the Positive and Negative Symptom Scale (PANSS), and a score of 
≤4 on the PANSS conceptual disorganization. (3) Currently, treatment 
involves atypical antipsychotic drugs, with their equivalent doses calculated 
using the defined daily dose method. (4) Individuals aged 18 to 50 years. (5) 
Educated at the primary school level or higher, and able to comprehend and 
collaborate to finish the trial. Exclusion criteria: (1) Patients are undergoing 
the acute phase of the disease and cannot cooperate in completing the examination 
and operational tasks under guidance. (2) Organic brain lesions, intellectual 
disabilities, or other severe physical illnesses. (3) Currently undergoing other 
neurostimulation therapies or evidence-based psychotherapy. (4) There are 
indications related to contraindications for HD-tDCS. (5) There are visual 
impairments or significant eye diseases, such as color blindness, color weakness, 
cataracts, etc. (6) Substance abuse and addiction. (7) Women who are pregnant or 
breastfeeding.

Clinical professionals who are qualified will conduct the evaluation of 
potential participants using the inclusion and exclusion criteria. Eligible 
individuals will receive comprehensive verbal and written details about the 
study’s benefits, risks, and precautions from psychiatrists. Upon consenting to 
participate, both the participants and their legal guardians are required to 
provide their signatures on an informed consent form. The trial 
will be carried out according to the 2013 Standard Protocol Items: Recommendations for Interventional Trials (SPIRIT) statement guideline for trial 
protocols [49]. See Table 1 and **Supplementary Material**.

**Table 1. S3.T1:** **World Health Organization trial registration data set related 
to this study**.

Data category	Information
Primary Registry and Trial Identifying Number	ChiCTR2500102731
Date of Registration in Primary Registry	19. May. 2025
Secondary Identifying Numbers	N/A
Source(s) of Monetary or Material Support	The Second Affiliated Hospital of Xinxiang Medical University, Henan Mental Hospital
Primary Sponsor	[name]. Ph.D., The Second Affiliated Hospital of Xinxiang Medical University, Henan Mental Hospital, [name]
Secondary Sponsor(s)	N/A
Contact for Public Queries	[name], The Second Affiliated Hospital of Xinxiang Medical University, Henan Mental Hospital, [contact]
Contact for Scientific Queries	[name]. Ph.D., The Second Affiliated Hospital of Xinxiang Medical University, Henan Mental Hospital, [contact]
Public Title	Efficacy and mechanisms underlying MRI-guided high-definition transcranial direct current stimulation combined with computerized cognitive remediation therapy for improving cognitive impairments in schizophrenia: study protocol for a randomized controlled trial
Scientific Title	Efficacy and mechanisms underlying MRI-guided high-definition transcranial direct current stimulation combined with computerized cognitive remediation therapy for improving cognitive impairments in schizophrenia: study protocol for a randomized controlled trial
Countries of Recruitment	China
Health Condition(s) or Problem(s) Studied	Schizophrenia
Intervention(s)	High-definition transcranial direct current stimulation (HD-tDCS) and/or computerized cognitive remediation therapy (CCRT)
Inclusion and Exclusion Criteria	Inclusion criteria:
	(1) According to Diagnostic and Statistical Manual of Mental Disorders, Fifth Edition (DSM-5), the individual meets the clinical criteria for schizophrenia.
	(2) Patients who maintain stability with oral antipsychotic medication are defined by the following criteria: a score of ≤5 on the items of exaggeration, delusion, suspiciousness/victimization, and hallucinatory behavior in the Positive and Negative Symptom Scale (PANSS), and a score of ≤4 on the PANSS conceptual disorganization.
	(3) Currently, treatment involves atypical antipsychotic drugs, with their equivalent doses calculated using the defined daily dose method.
	(4) Individuals aged 18 to 50 years.
	(5) Educated at the primary school level or higher, and able to comprehend and collaborate to finish the trial.
	Exclusion criteria:
	(1) Patients are in the acute phase of the disease and cannot cooperate in completing the examination and operational tasks under guidance.
	(2) Organic brain lesions, intellectual disabilities, or other severe physical illnesses.
	(3) Currently undergoing other neurostimulation therapies or evidence - based psychotherapy.
	(4) There are indications related to contraindications for HD-tDCS.
	(5) There are visual impairments or significant eye diseases, such as color blindness, color weakness, cataracts, etc.
	(6) Substance abuse and addiction.
	(7) Women who are pregnant or breastfeeding.
Study Type	Interventional
	Allocation: randomized
	Masked: double blind
	Primary purpose: schizophrenia intervention
Date of First Enrollment	June 2025
Sample Size	48
Recruitment Status	Pending
Primary Outcome(s)	(1) MATRICS Consensus Cognitive Battery (MCCB)
	(2) Brief Psychiatric Rating Scale (BPRS)
	(3) Positive and Negative Syndrome Scale (PANSS)
Key Secondary Outcomes	(1) Clinical Global Impressions (CGI)
	(2) Social Disability Screening Schedule (SDSS)
	(3) Schizophrenia Quality of Life Scale (SQLS)
	(4) Magnetic Resonance Imaging (MRI)
	(5) General Information Questionnaire (GIQ)
	(6) Adverse Reaction Scale (ARS)
	(7) Serum levels of Brain-Derived Neurotrophic Factor (BDNF)
	(8) Serum levels of Glial Cell Line-Derived Neurotrophic Factor (GDNF)
Ethics Review	Approved (Approval Number: XYEFYLL-2025-15)
	Approval Date: 17 February 2025
	The Second Affiliated Hospital of Xinxiang Medical University. [contact], [name]
Completion date	Pending
Summary Results	Pending
IPD sharing statement	N/A

The research could be halted under the following conditions: (1) the occurrence 
of an unexpected medical emergency; (2) the emergence of severe side effects or 
adverse events that preclude the continuation of the study; or (3) the withdrawal 
of informed consent by the participant or their family. It is imperative that 
participants have maintained a stable dose of antipsychotic medication at least 
two weeks, and that this dosage remains unchanged throughout the study duration. 
During the therapy, participants will continue to receive their routine daily 
treatment.

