**Methods::**

Schizophrenia patients will be randomly assigned to one of 4 groups: HD-tDCS + CCRT group (Group 1), HD-tDCS group (Group 2), CCRT group (Group 3), and a control group (Group 4). The central electrode will be personalized using magnetic resonance imaging (MRI)-guided localization in the medial prefrontal cortex (mPFC). CCRT includes 6 therapeutic modules and 10 distinct tasks. Both HD-tDCS and CCRT will be administered once daily, 5 days per week, for 4 consecutive weeks, culminating in a total of 20 sessions. Assessments will occur at baseline (T0), after 10 sessions (T1), after 20 sessions (T2), and after 6 months of follow-up (T3). The primary outcome measure is the change in cognition. We will employ multimodal MRI, serum concentrations of brain-derived neurotrophic factor (BDNF) and glial cell line-derived neurotrophic factor (GDNF) to explore the underlying mechanisms.

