activity [37]. Importantly, prefrontal-temporal tDCS has been shown to modulate 
dysfunctional network connectivity in patients with schizophrenia, underscoring 
the potential of neuromodulation to target circuit-level deficits [38]. Moreover, 
tDCS not only modulates the activity and connectivity of cortical and subcortical 
brain networks but also influences blood concentrations of biomarkers such as 
brain-derived neurotrophic factor (BDNF) and glial cell line-derived neurotrophic 
factor (GDNF). These systemic alterations collectively form the biological basis 
for its therapeutic effects [39]. BDNF and GDNF function as critical biomarkers 
for synaptic plasticity, a process involved in the pathogenesis and treatment of 
schizophrenia [40]. The hypothesized mechanisms underlying HD-tDCS, particularly 
its enhancement of long-term memory, include the upregulation of BDNF expression, 
activation of its signaling pathway, and improved synaptic plasticity [41]. 
Similarly, studies on CCRT have demonstrated its effectiveness in enhancing 
cognitive function in schizophrenia, accompanied by observed increases in serum 
GDNF levels [42]. Moreover, the literature also proposes that serum BDNF and GDNF 
levels might represent the central nervous system’s BDNF and GDNF expression 
profile [43, 44]. BDNF is essential for neuronal synthesis, 
differentiation, maintenance, and survival. Studies have demonstrated a 
correlation between decreased peripheral blood BDNF levels and cognitive 
impairments, such as attention deficits, in individuals with schizophrenia 
[45, 46, 47]. GDNF levels have been associated with working memory performance and 
attention deficits [48]. As far as we know, no research has investigated the 
combined effects of magnetic resonance imaging (MRI)-guided HD-tDCS targeting 
mPFC and CCRT on cognitive deficits, nor the biological mechanisms underlying 
their combined use in treating schizophrenia.

The current study aims to achieve three primary objectives. The primary aim of 
this study is to evaluate the synergistic effects of HD-tDCS and CCRT on 
cognitive abilities and clinical symptoms through a randomized controlled trial. 
We hypothesize that the combined HD-tDCS and CCRT intervention will result in 
greater cognitive improvement in individuals with schizophrenia compared to 
either intervention alone. The secondary aim is to evaluate the long-term impacts 

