### 2.9 Outcome

The primary outcome measure used in this research is the MATRICS Consensus 
Cognitive Battery (MCCB), which is a crucial tool for assessing cognitive 
deficits in schizophrenia. It evaluates seven distinct cognitive domains: working 
memory, abstract thinking, attention/vigilance, processing speed, visual 
learning, verbal/visual learning, reasoning and problem-solving. The battery 
comprises the following subtests: (1) Trail Making Test A (TMT-A), (2) Symbol 
Coding, (3) Hopkins Verbal Learning Test-Revised (HVLT-R), (4) Digit Span Test 
(DST), (5) Stroop Color-Word Test, (6) Spatial Span Test (derived from the 
Wechsler Memory Scale III, WMS-III), (7) Verbal Fluency Test (VFT), (8) Mazes, 
(9) Brief Visuospatial Memory Test-Revised (BVMT-R), and (10) Continuous 
Performance Test-Identical Pairs (CPT-IP).

Secondary outcome measures include the Brief Psychiatric Rating Scale (BPRS), 
the PANSS, the Clinical Global Impression 
(CGI) scale, the Social Disability Screening Schedule (SDSS), the Schizophrenia 
Quality of Life Scale (SQLS), and fMRI. Specifically, the general information 
questionnaire is utilized to collect basic information about the patients. BPRS 
primarily assesses the severity of psychotic symptoms, with total scores ranging 
from 18 to 126, where higher scores reflect more severe symptoms. PANSS is used 
to evaluate the presence and severity of various symptoms. CGI scale is applied 
to assess the patient’s overall condition and therapeutic efficacy. SDSS measures 
the extent of social functional deficits. SQLS is designed to evaluate the 
quality of life in schizophrenia. For detailed information, please see Table 2.

**Table 2. S3.T2:** **Schedule of enrollment, interventions, assessments, and visits 
of patients**.

	Recruitment	Baseline	Assessments		
			Weekend 2	Weekend 4	6-month follow-up
Time point		T0	T1	T2	T3
Prescreening for eligibility, consenting and clinical interview					
Recruitment					
Eligibility screening	√				
Informed consent	√				
Allocation	√				
Primary outcome assessment					
MCCB		√	√	√	√
Second outcome assessment					
BPRS		√	√	√	√
PANSS		√	√	√	√
CGI		√	√	√	√
SDSS		√	√	√	√
SQLS		√	√	√	√
GIQ		√			
MRI		√	√	√	√
Blood sample collection (BDNF and GDNF levels)		√		√	√
Safety					
ARS			√	√	

A checkmark (√) indicates the time point at which each assessment is 
carried out. MRI, magnetic resonance imaging.

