to evaluate the robustness of our findings. Line charts will be employed to 
visualize the data, offering a clear depiction of outcome value trends across 
time points. Given the repeated-measures nature of the data, we will utilize 
statistical methods suitable for this design. In addition to the mixed-effects 
models, we will explore non-parametric repeated-measures approaches where 
applicable. These methods are suitable for analyzing between-group differences at 
specific time points and changes within groups over time for both primary and 
secondary outcomes. Moreover, the Likelihood Ratio Test will be used to 
specifically assess the effect of the therapy. The Bonferroni correction will be 
employed to adjust *p*-values, addressing the issue of multiple comparisons from 
evaluations at different time points.

To further elucidate the underlying mechanisms, we will conduct correlation 
analyses to investigate the relationships between alterations in neuroimaging 
metrics, serum levels of BDNF/GDNF, and cognitive performance scores in 
participants. Additionally, we intend to utilize mediation analysis models to 
assess whether intervention-induced changes in brain activity and/or BDNF/GDNF 
levels mediate improvements in cognitive outcomes. Moreover, we will perform an 
exploratory analysis of the CCRT metrics (e.g., task accuracy, reaction time) to 
compare cognitive performance during training between the HD-tDCS + CCRT group 
(Group 1) and the CCRT group (Group 3). This analysis could clarify the immediate 
neuroenhancing potential of concurrent HD-tDCS.

A stable antipsychotic medication regimen will be required for all patients, 
requiring consistent dosing for a minimum of two weeks prior to the trial and 
maintaining this regimen unchanged throughout the study period. This protocol 
will be implemented to minimize confounding effects on clinical outcomes, in 
accordance with recommendations from previous literature [52]. The Defined Daily 
Dose (DDD) methodology will be utilized to standardize antipsychotic medication 
doses across study groups. This involves converting administered doses into DDD 
units following randomization to ensure pharmacological equivalence. To account 
for dosing variability and maintain the accuracy of results, DDD values will be 
incorporated as a covariate in all statistical models. All collected data will be 

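### Table 1 lists three primary outcomes and section 2.9 lists one, and no rule across outcomes is stated, so the two lists must be made to agree before unblinding.

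*Protocol article*

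**What the plan says.** The protocol article names its primary outcome in several places, and they differ.

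- **Abstract, Methods:** "The primary outcome measure is the change in cognition".
- **Introduction, aims:** the primary aim is the synergistic effect of the two treatments on "cognitive abilities and clinical symptoms through a randomized controlled trial". Symptoms stand beside cognition here, although the hypothesis in the next sentence concerns cognition only.
- **Section 2.2, Table 1 (registration data set):** three entries stand under primary outcomes: "1) MATRICS Consensus Cognitive Battery (MCCB", "2) Brief Psychiatric Rating Scale (BPRS" and "3) Positive and Negative Syndrome Scale (PANSS".
- **Section 2.9:** "The primary outcome measure used in this research is the MATRICS Consensus" Cognitive Battery. The next paragraph begins "Secondary outcome measures include the Brief Psychiatric Rating Scale (BPRS" and goes on to name the PANSS as well.
- **Table 2:** MCCB alone is in the primary block; BPRS and PANSS are in the secondary block.

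On error control, section 2.11 applies Bonferroni for one purpose, "addressing the issue of multiple comparisons from" evaluations at different time points, and sets significance at p < 0.05. It plans the sample size on a single alpha of 0.05 with power 0.80 and f = 0.25, which gives 36 participants, or 48 after 20% dropout in equal groups. It adds the HD-tDCS × CCRT interaction to the models in order to assess synergy. The Introduction and section 3 state the hypothesis differently: the combination does better than either treatment alone.

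**The concern.** Both lists are in the current text, so no later analysis plan can make both true. The choice between them decides what counts as a positive trial. Under section 2.9, a benefit on symptoms without a benefit on the MCCB is a secondary result. Under Table 1 it could be presented as success on a primary outcome. The stated Bonferroni correction works across visits within an outcome and does nothing across outcomes. The document gives no hierarchy, no requirement that all three succeed and no split of alpha.

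Two things are at stake. One is the false-positive rate of the primary claim if Table 1 is followed. The other is credibility: if the lists still differ when the data are unblinded, whichever one is then used can be seen as chosen to suit the results.

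**Working it through.** **1. The plan's own sample size.** Inputs from section 2.11: F-test, repeated-measures ANOVA, alpha 0.05, power 0.80, f = 0.25. The design has g = 4 groups and m = 4 assessments (T0 to T3). The document gives neither the correlation between repeated measures nor the sphericity factor; I assume 0.5 and 1. For the group-by-time test, λ = f²·N·m/(1 − ρ), df1 = (g − 1)(m − 1) and df2 = (N − g)(m − 1).

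- At N = 36: λ = 0.0625 × 36 × 4 / 0.5 = 18, df = 9 and 96, power 82.5%.
- 36 is the smallest number in equal groups that reaches 80%. Then 36 / 0.8 = 45, which becomes 48 in four equal groups.

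The stated 36 and 48 therefore reproduce, for one outcome tested at 0.05.

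**2. Simple bounds for three primaries.** Suppose each outcome is held at 5% over its visits and any one can carry the claim. The family-wise error is at most 3 × 0.05 = 15%. If the outcomes are independent it is 1 − 0.95³ = 14.3%. With a common correlation (assumed) it is 12.5% at 0.5, 9.8% at 0.8 and 8.3% at 0.9.

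**3. With the visits modelled.** Bonferroni over correlated visits is conservative, so step 2 somewhat overstates the error. I simulated correlated normal test statistics at three post-baseline visits, each tested two-sided at 0.05/3 = 0.0167, with visit correlation 0.6. The divisor of three and all correlations are assumptions. The first results column is the HD-tDCS × CCRT interaction. The second is Group 1 against Group 2 and against Group 3, with either win counting; those two contrasts share Group 1 and so correlate at 0.5.

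| Outcomes tested | Interaction | Group 1 vs 2 and vs 3 |
|---|---|---|
| One MCCB score | about 4% | about 8% |
| Three primaries, all pairs 0.3 | about 12% | about 21% |
| Three primaries, all pairs 0.5 | about 11% | about 19% |
| Three primaries, MCCB 0.2 with each scale, BPRS-PANSS 0.8 | about 10-11% | about 19% |
| Three primaries, all pairs 0.8 | about 9% | about 15% |

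The third and fourth rows of three primaries matter because BPRS and PANSS both rate psychotic symptoms and may well be highly correlated.

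**4. Cost of controlling three primaries.** Splitting alpha gives 0.05/3 = 0.0167. Under the step 1 assumptions, power with 36 evaluable falls from 82.5% to 68.4%. Reaching 80% needs 44 evaluable, and 44 / 0.8 = 55, which becomes 56 in equal groups (14 per group). If all 48 were retained, power at 0.0167 would be 86.4%, so the shortfall appears once the planned dropout occurs.

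**The case against.** The strongest reply is that the intended primary is clear. The abstract, section 2.9 and Table 2 agree on cognition or the MCCB, and the outlier is a registration table plus one sentence of aims. On that reading, with one score and one contrast, Bonferroni over visits keeps the error at about 4%, within the nominal 5%. This stands. It makes inflation conditional on Table 1 governing, and it shows which way the lists are most easily reconciled. It does not remove the contradiction, because Table 1 is presented as the registered data set.

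A reader might infer that the trial may declare success on any scale, MCCB domain, visit or pair of groups, and reach a much larger error rate by counting every such test. The document does not support that. No passage says that any one outcome suffices. Section 2.9 lists the domains to describe what the battery covers and does not make them separate endpoints. No passage makes all six group comparisons a primary claim, and section 2.11 ties synergy to the interaction. Requiring success on all three outcomes would not inflate alpha at all.

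It is also fair that the exact MCCB score, the primary visit and the testing scheme for secondary outcomes may be left to the full protocol or analysis plan. Their absence from an article is not counted as a fault here. The visit is in any case partly indicated: six-month effects belong to the secondary aim, and section 3 points to the end of four weeks of treatment.

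**Conclusion.** The point holds as an internal contradiction with a conditional consequence. Table 1 and section 2.9 cannot both be right about the primary outcomes, and the one multiplicity rule does not cover the case of three. If Table 1 governs and any one outcome can carry the claim, the false-positive chance on the interaction is about 9-12%, against about 4% for one MCCB score. These figures rest on the assumed three visits, visit correlation 0.6 and outcome correlations 0.2-0.8. If all three outcomes must succeed, alpha is not inflated and power falls instead.

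It would be too strong to conclude that the trial has no 5% error rate under any reading: section 2.9 with one score and one contrast has one. It would also be wrong to conclude that the sample size is miscalculated, since 36 reproduces for a single outcome at 0.05.

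A narrower issue remains about the contrast. The interaction asks whether the joint effect differs from the sum of the separate effects; the hypothesis asks whether the combination beats each treatment alone. These can give different answers, and the document does not say which is the primary test.

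**What to change.** Before unblinding, make Table 1, section 2.9, Table 2 and the primary aim agree.

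- **Simplest route**, consistent with the abstract, section 2.9 and the existing sample size: keep the MCCB as sole primary, as one overall score at the end of treatment (T2). Move BPRS and PANSS to secondary in Table 1, and in the registry entry if it matches Table 1; the live record was not available to check. Reword the primary aim so that clinical symptoms are a secondary objective. The planned alpha and the 36 and 48 then need no change on this account.
- **Alternative:** keep three primaries and state the rule, either that all must succeed or how alpha is divided. Restate the power to match: about 68% with 36 evaluable at 0.05/3, or 56 randomised to restore 80% after dropout, under the assumptions given.
- **In either case**, state whether the primary test is the HD-tDCS × CCRT interaction or the combination against each treatment alone. If the latter, say whether both comparisons must succeed.

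The cost is small but is more than an edit. Changing the listed primaries is a significant amendment, so section 2.15 requires ethics review first, then written notice to the parties and a record on the registry, which should be dated. The scientific price of the simplest route is that fewer results can be called confirmatory.

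### Table 1 lists three primary outcomes (MCCB, BPRS, PANSS), while the Abstract, section 2.9 and Table 2 make cognition (MCCB) the only one, and no rule covers several primaries

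*Protocol article*

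**What the plan says.** **Three primaries.** In section 2.2, Table 1 (the WHO registration data set) has three entries under primary outcomes: "1) MATRICS Consensus Cognitive Battery (MCCB"), "2) Brief Psychiatric Rating Scale (BPRS") and "3) Positive and Negative Syndrome Scale (PANSS"). Neither symptom scale appears among its key secondary outcomes.

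**One primary.** The Abstract states: "The primary outcome measure is the change in cognition". Section 2.9 opens with "The primary outcome measure used in this research is the MATRICS Consensus" Cognitive Battery, and continues: "Secondary outcome measures include the Brief Psychiatric Rating Scale (BPRS"), with the PANSS next in that list. Table 2 makes the same split.

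**Aim.** The Introduction's primary aim concerns effects on "cognitive abilities and clinical symptoms through a randomized controlled trial". The hypothesis that follows speaks only of cognitive improvement.

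**Analysis.** Section 2.11 sizes the trial with one repeated-measures F-test at alpha 0.05 and applies Bonferroni to evaluations at different time points. It says nothing about several primary outcomes.

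**Other outcomes.** Table 1's key secondary list includes "5) General Information Questionnaire (GIQ"). Section 2.9 describes this as a form for basic patient information, and Table 2 schedules it at T0 only. Table 1 also lists ARS as key secondary, while Table 2 places it under safety.

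**The concern.** BPRS and PANSS cannot be both primary and secondary. Suppose the MCCB shows no effect and a symptom scale does. Table 1 would let the trial report success on a primary outcome; section 2.9 would not. A reader of the final report could not tell which definition was in force, and the choice could be made after the results are known.

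The three-primary reading is not confined to one table row, because the primary aim also reaches clinical symptoms. Nor does the analysis section settle it: there is no rule that all three must succeed, no split of alpha and no order of testing.

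**Working it through.** **1. The plan's own sample size.** Section 2.11 gives f = 0.25, alpha = 0.05, power 0.80 and a required N of 36. The article does not state which effect was tested, the correlation between repeated measures, or the sphericity correction. Assume the group-by-time interaction, 4 groups, 4 measurements, correlation 0.5 and epsilon 1:

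- noncentrality = f² × N × m / (1 − ρ) = 0.0625 × 36 × 4 / 0.5 = 18
- df1 = (4 − 1)(4 − 1) = 9; df2 = (36 − 4)(4 − 1) = 96
- power = 0.825, and 36 is the smallest multiple of 4 that reaches 0.80
- dropout: 36 / (1 − 0.20) = 45, rounded up to equal groups = 48

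So 36 and 48 reproduce for one outcome tested at 0.05. (A within-subject effect with 4 groups and 2 measurements also gives 36, so the match does not prove which effect was meant.)

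**2. False-positive rate if any of the three counts as primary.** Each outcome is taken as one score with one two-sided test at 0.05. If the tests are independent:

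- any of three: 1 − 0.95³ = 0.1426
- BPRS or PANSS: 1 − 0.95² = 0.0975

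The documents give no correlations between the test statistics. Simulating three correlated normal statistics (2,000,000 draws) over an assumed range gives:

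| Assumed correlations | Any of three | BPRS or PANSS |
|---|---|---|
| all 0 | 14.3% | 9.8% |
| all 0.5 | 12.5% | 9.0% |
| all 0.7 | 11.0% | 8.4% |
| BPRS-PANSS 0.8, MCCB with each 0.3 | 12.1% | 7.8% |
| BPRS-PANSS 0.9, MCCB with each 0.3 | 11.4% | 7.0-7.1% |

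A single named scale stays at 5%.

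**3. The two ways to reconcile.**

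- MCCB as sole primary: alpha stays 0.05, and 36 (48 recruited) stands.
- Three primaries with any one sufficient, Bonferroni at 0.05 / 3 = 0.0167 each: the family-wise rate is 1 − (1 − 0.0167)³ = 4.9% if independent. Under the step 1 assumptions, power at 36 completers falls from 0.825 to 0.684. N rises from 36 to 44; 44 / 0.80 = 55, or 56 with equal groups.

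**The case against.** The best defence is that the intent is clear. The Abstract, section 2.9, Table 2 and the hypothesis all point to cognition, so Table 1 looks like a mistaken row. That stands as evidence of which version to keep. It does not remove the contradiction, and an unseen analysis plan cannot either, because both classifications are in the current text.

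Several stronger readings are tempting, and the documents do not support them:

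- **A symptom finding carries an 11-14% false-positive rate.** That range is the chance that any of the three, MCCB included, is falsely positive. For BPRS or PANSS it is about 7-10%.
- **The trial has adopted an any-one-suffices rule.** No such rule is stated. The rates show what would follow if Table 1 were used that way.
- **GIQ, BDNF and GDNF are missing from section 2.9's secondary outcomes.** They are missing only from its prose. Table 2, in the same section, lists all three under its secondary heading. Of Table 1's additional entries, only ARS has a different status.
- **Symptoms are a poor primary target.** The Introduction cites a combined-treatment study without a significant symptom effect, but adds that its sample was small. Entry also allows scores up to 5 on PANSS positive items. This is a preference, not an error in the plan.
- **The registry entry is wrong.** The entry itself is not at hand; only Table 1's version of it can be seen.

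**Conclusion.** The article contradicts itself on what the primary outcome is, and it must be reconciled. This finding depends on no calculation.

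The size is conditional. If any of the three outcomes could be claimed as primary at an unadjusted 0.05, the chance of at least one false-positive primary would be about 11-14%, against a nominal 5%. For the symptom pair it would be about 7-10%. Both ranges rest on assumed correlations and one test per outcome.

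The sample size is not put in doubt by this point: with the MCCB as sole primary, 36 analysed and 48 recruited are unaffected.

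**What to change.** - In Table 1, name the MCCB as the only primary outcome and list BPRS and PANSS as secondary, as in section 2.9 and Table 2.
- Align the Introduction's primary aim with this, keeping clinical symptoms as a secondary aim.
- Remove GIQ as an outcome from Table 1 and from the secondary heading of Table 2. A form completed only at baseline cannot measure a treatment effect.
- Give ARS one status, either key secondary or safety, in both tables.
- Check the registry entry. If it already names the MCCB alone, only the article needs correcting. If it lists three primaries, amend it by the route in section 2.15, and date and disclose this as a change of primary outcome made before outcome data are analysed. A promise to act before unblinding is weaker, since section 2.4 gives the principal investigator the allocation during the trial.

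**Cost:** a text correction and, if needed, an ethics submission and registry update. No more participants are required. Symptom effects could be claimed only as secondary, and any change after the registration of 19 May 2025 would have to be disclosed.
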